## **8.1 Screening**

Each subject will be screened prior to enrollment on VAX-103-01. Re-screens will not be permitted.

### **8.1.1 Eligibility screening**

Results of below screening measurements will be available as source data at the study site and will not be recorded within the eCRF.

#### **8.1.1.1 Hepatitis screen, HIV screen**

All participants will be screened for HBsAg and, if standard local practice, Hepatitis B core antigen (HBcAg). Screening for Hepatitis C will be based on Hepatitis C virus (HCV) antibodies and if positive, HCV RNA levels should be determined.

Evaluation for HIV seropositivity will be performed, and, if positive, confirmation by a second technique available at the laboratory site e.g. Western blot. Appropriate counseling will be made available by the investigator in the event of a positive confirmatory test. Notification of state and federal authorities, as required by law, will be the responsibility of the investigator.

#### **8.1.1.2 Alcohol test, Drug screen**

Participants will be tested for substances of abuse (e.g. alcohol, amphetamines, barbiturates, benzodiazepines, cannabinoids, cocaine and opiates). A positive screen for marijuana is not considered to be a screen-failure unless it is within 7 days of enrollment or the investigator believes there to be a history of abuse.

### **8.1.2 Information to be collected on screening failures**

Participants who sign an informed consent form and subsequently found to be ineligible prior to randomization will be considered a screen failure. The reason for screen failure should be recorded on the appropriate eCRF. The demographic information, informed consent, and inclusion/exclusion pages must also be completed for screen failure participants. No other data will be entered into the clinical database for participants who are screen failures, unless the participant experienced a SAE during the screening phase (see Section 10 [SAFETY MONITORING AND REPORTING](#) for SAE reporting details). If the participant fails to be randomized, the study team should document the reason within the appropriate eCRF.

Participants who are randomized and fail to start treatment, e.g. participants randomized in error, will be considered an early terminator. The reason for early termination should be recorded on the appropriate eCRF.

## **8.2 Participant demographics/other baseline characteristics**

Participant demographics: date or year of birth (if permitted), sex, race, predominant ethnicity (if permitted) and relevant medical history/current medical conditions (until date of signature of informed consent) will be recorded in the eCRF. Where possible, the diagnosis and not symptoms should be recorded.

All prescription medications, over-the-counter drugs and significant non-drug therapies prior to the start of the study must be documented. See the protocol Section 6.2.1 Concomitant Therapy for further details on what information must be recorded on the appropriate page of the eCRF.

### 8.3 Efficacy

No efficacy assessments are planned for this study, and immunogenicity samples will be collected at the time-points defined in the assessment schedule (Table 5).

Immunogenicity samples will be obtained and evaluated in all participants at all dose levels, including the placebo group. In order to better define the immunogenicity profile, the timing of the sample collection may be altered based on emergent data.

Immunogenicity assessments are described in Section 8.5.1 Immunogenicity.

#### 8.3.1 Appropriateness of efficacy assessments

Not applicable.

### 8.4 Safety, Reactogenicity and Tolerability

Safety assessments are specified below (Table 6) with the assessment schedule detailing when each assessment is to be performed. Each clinical research site must have epinephrine on hand and the staff should administer in case of anaphylaxis. Should anaphylaxis occur, the site staff should treat according to institutional guidelines.

For details on AE collection and reporting, refer to Section 10 SAFETY MONITORING AND REPORTING.

**Table 6: Assessment Specification**

| Assessment           | Specification                                                                                                                                                                                                                                                                                                                                                                                                                                                                                                                                                                                                                                                                                                                                                                                                                                                                                                                                                                                                                                                                                                                                                                                                                                                                                                                  |
|----------------------|--------------------------------------------------------------------------------------------------------------------------------------------------------------------------------------------------------------------------------------------------------------------------------------------------------------------------------------------------------------------------------------------------------------------------------------------------------------------------------------------------------------------------------------------------------------------------------------------------------------------------------------------------------------------------------------------------------------------------------------------------------------------------------------------------------------------------------------------------------------------------------------------------------------------------------------------------------------------------------------------------------------------------------------------------------------------------------------------------------------------------------------------------------------------------------------------------------------------------------------------------------------------------------------------------------------------------------|
| Physical examination | 
A complete physical examination will include the examination of general appearance, skin, neck (including thyroid), eyes, ears, nose, throat, lungs, heart, abdomen, back, lymph nodes, extremities, vascular, and neurological. If indicated based on medical history and/or symptoms, rectal, external genitalia, breast, and pelvic exams will be performed. A complete physical examination will be at screening and final study or early termination visits.
 
An abbreviated physical exam will include the examination of general appearance, axillary and cervical lymph nodes, site of MAP, any other body system directed by participant's symptoms, and vital signs (blood pressure [SBP and DBP] and pulse). An abbreviated physical exam will be at visits starting from post screening and before final study visit except where a complete physical examination is required (see above).
 
Information for all physical examinations must be included in the source documentation at the study site. Clinically relevant findings that are present prior to signing informed consent must be recorded on the appropriate eCRF that captures medical history. Significant findings made after signing informed consent which meet the definition of an AE must be recorded as an adverse event.
 |
| Vital signs          | 
Vital signs will include the collection of oral temperature (recorded in °C), blood pressure (BP) and pulse measurements. The same method for obtaining temperature should be used for the duration of the trial.
 
After the participant has been sitting for 5 minutes, with back supported and both feet placed on the floor, systolic and diastolic BP will be measured using an automated validated device, e.g. OMRON with an appropriately sized arm cuff. In case the arm cuff sizes
                                                                                                                                                                                                                                                                                                                                                                                                                                                                                                                                                                                                                                                                                                                                                                                                                       |

|                                                                       |                                                                                                                                                                                                                                                                                                                                                                                                                                                                                                                                                                                                                                                                                                                                                                                                          |
|-----------------------------------------------------------------------|----------------------------------------------------------------------------------------------------------------------------------------------------------------------------------------------------------------------------------------------------------------------------------------------------------------------------------------------------------------------------------------------------------------------------------------------------------------------------------------------------------------------------------------------------------------------------------------------------------------------------------------------------------------------------------------------------------------------------------------------------------------------------------------------------------|
|                                                                       | 
available are not large enough for the participant's arm circumference, a sphygmomanometer with an appropriately sized cuff may be used.
 
If vital signs are out-of-range at screening and/or baseline (see Exclusion Criteria Section 5 STUDY POPULATION of the protocol for details), two additional readings can be obtained, so that a total of three consecutive assessments are made, with the participant seated quietly for approximately five minutes preceding each repeat assessment. The last reading must be within the ranges provided in the eligibility criteria in order for the participant to qualify.
 
In case of repeated vital assessments, the eCRF should contain the qualifying results.
                                                     |
| Safety Laboratory Assessments                                         | Hematology, chemistry, coagulation parameters and urinalysis are obtained from the site's local laboratory (See Table 5 ).                                                                                                                                                                                                                                                                                                                                                                                                                                                                                                                                                                                                                                                               |
| Height and weight                                                     | 
Height is obtained in centimeters (cm) and body weight is obtained in kilograms (kg) and rounded to the nearest 0.1 kg. Weight is obtained in indoor clothing, without shoes.
 
Body mass index (BMI) will be calculated using the following formula:
 $\text{BMI} = \text{Body weight (kg)} / [\text{Height (m)}]^2$ 
Indicate whether rounding should be done to nearest whole number or not (e.g. if range in inclusion/exclusion criteria is 18-30 kg/m^2 and calculated BMI is 30.44, discuss with Medical Lead whether the BMI value can be rounded to 30 kg/m^2).
 
The Screening Visit height measurement will be used for BMI calculations throughout the study.
                                                                                      |
| Photographs of treatment site                                         | Site staff will take a picture of the treatment site and upload to a secure file server at each scheduled interval.                                                                                                                                                                                                                                                                                                                                                                                                                                                                                                                                                                                                                                                                                      |
| Local Reactogenicity and Tolerability and Systemic Safety Assessments | 
Local reactogenicity and tolerability, specifically, pain, induration, tenderness, erythema and edema will be assessed according to Appendix 1: Local Tolerability Scoring.
 
Other local tolerability measures including bruising, itching, skin flaking and application site pigmented skin coloration will be assessed as outlined in Appendix 2: Other Local Tolerability Scoring.
 
Systemic safety measures will be assessed as outlined in Appendix 3: Systemic Toxicity Grading Scales.
 
All assessments will take place according to Table 5.
 
If an AE is reported by telephone for which an in-clinic assessment may be warranted, an unscheduled (optional) visit can be performed at any time.
 |
| Medical Questioning                                                   | The investigator will assess the participant for any reported AEs and ensure approval is provided before discharging the participant from the site.                                                                                                                                                                                                                                                                                                                                                                                                                                                                                                                                                                                                                                                      |

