## 2 OBJECTIVES

**Table 1: Objectives and related endpoints**

| Objective(s)                                                                                                                 | Endpoint(s)                                                                                                                                                    |
|------------------------------------------------------------------------------------------------------------------------------|----------------------------------------------------------------------------------------------------------------------------------------------------------------|
| Primary objective(s)                                                                                                         | Endpoint(s) for primary objective(s)                                                                                                                           |
| 
 
To describe the safety, reactogenicity and tolerability profiles of VX-103
 
 | 
 
Changes in physical exams, vital signs, laboratory parameters of hematology, clinical chemistry, urinalysis,
 
 |

| delivered as a single MIMIX MAP immunization in healthy adults $\geq 18$ -39 years of age for two influenza vaccine dose levels, fractional H1 vaccine dose level 7.5 $\mu\text{g}$ and standard H1 vaccine dose level 15 $\mu\text{g}$ vs placebo.                                                                                                                                                                                                                                                                                                       |  | AEs, and local and systemic solicited and unsolicited reactogenicity event(s)                                                                                                                                                                                                                                                                                                                                                                                                                                                                                                                                         |  |

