## 5.1 Inclusion Criteria

1. Male or female aged 18 – 39 years, inclusive at screening.
2. Provide written informed consent to participate in the trial.
3. Participants who, in the opinion of the investigator, can and will comply with the requirements of the protocol.
4. Healthy participants without acute or chronic, clinically significant pulmonary, cardiovascular, hepatic or renal functional abnormality
  - a. as determined by medical history, physical exam, laboratory screening
5. Body Mass Index 18-35 kg/m^2, inclusive, at screening.
6. Females should fulfill one of the following criteria:
  - At least one year post-menopausal,
  - Surgically sterile,
  - Will use oral, implantable, transdermal or injectable contraceptives during the screening window and until 60 days after vaccination
  - Willing to use a highly effective method of contraception approved by the Investigator for study duration and until 60 days after vaccination
7. Women of childbearing potential must have a negative urine pregnancy test at screening and within 24 hours preceding receipt of vaccination.
8. Male participants must be surgically sterile (e.g., vasectomy) or agree to practice highly effective method of contraception from screening until 60 days after vaccination.
9. Vital signs within following range:
  - a. oral temperature <100.0°F (37.8°C),
  - b. pulse <100 bpm,
  - c. Systolic blood pressure (SBP) ≤ 150 to 85 mmHg
10. Clinical screening laboratory evaluations (White Blood Cells [WBCs], hemoglobin [Hgb], platelets [PLTs], Alanine Transaminase [ALT], Aspartate Transaminase [AST], Creatinine [Cr], Alkaline Phosphatase [ALP], Total Bilirubin [T. Bili], Lipase, Prothrombin Time [PT], Partial Thromboplastin Time [PTT]) are within acceptable normal reference ranges at the clinical laboratory being used or determined to not be clinically significant in the opinion of the investigator.

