#### **Adverse events**

All information obtained on AEs will be displayed by treatment group, ethnicity, and participant.

The number (and percentage) of participants with treatment-emergent AEs (events started on or after the dose of study medication or events present prior to start of treatment but increased in severity on or after the dose of study medication based on preferred term) will be summarized in the following ways:

- by treatment, ethnicity, primary system organ class and preferred term.
- by treatment, ethnicity, primary system organ class, preferred term and maximum severity

Separate summaries will be provided for study medication related AEs, death, SAEs, other significant AEs leading to discontinuation.

A participant with multiple AEs within a primary system organ class is only counted once towards the total of the primary system organ class.

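### The rule on repeated vital signs lets an out-of-range pre-dose reading stay out of the eCRF, so a pulse already graded before dosing can look new afterwards

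*Protocol*

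**What the plan says.** The vital-signs row of Table 6 (Protocol, section 8.4) covers readings that are out of range at screening and/or baseline. In that case "two additional readings can be obtained, so that a total of three consecutive assessments are made". Eligibility then turns on the final one: "The last reading must be within the ranges provided in the eligibility criteria in order for the participant to qualify". The row ends with the data-capture rule: "In case of repeated vital assessments, the eCRF should contain the qualifying results". No repeat rule is given for post-dose readings.

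The limits are in section 5.1, item 9: "pulse <100 bpm" and "Systolic blood pressure (SBP) ≤ 150 to 85 mmHg". There is no diastolic limit. In Appendix 3, Grade 1 tachycardia is 101–115 bpm. Systolic hypertension is Grade 1 at 141–150 mmHg, Grade 2 at 151–155 and Grade 3 above 155.

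Table 1 makes vital signs part of the primary endpoint: "Changes in physical exams, vital signs, laboratory parameters of hematology, clinical chemistry, urinalysis". The vital-signs paragraph of section 12.4.2 plans listings of all vital-sign data, flags for abnormal values, and summary statistics by group and visit.

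**The concern.** Pre-dose readings pass through a filter before they reach the database; post-dose readings do not. If the eCRF holds just the qualifying Day 1 value, every enrolled participant has tachycardia grade 0 at baseline by construction, because eligibility ends below 100 and grading begins at 101. Someone who read 104, then 102, then 97 before dosing is recorded as 97. A post-dose 104 is then listed and flagged beside a normal baseline, although the same value had been seen minutes before the patch was applied.

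For systolic pressure the same can happen only above 150 mmHg, that is, with a pre-dose Grade 2 or 3 value.

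This matters because the study is first-in-human, the primary objective is descriptive, and each arm has 15 participants, so one or two misread events would be visible. A statistical analysis plan can define baseline however it likes, but it cannot restore readings that were never entered.

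**Working it through.** The protocol gives no mean or standard deviation for vital signs, and section 12.8 rests the sample size on past practice, so there is no figure of its own to reproduce. The size below depends on assumptions, shown as a range.

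**Model for pulse, no treatment effect.** A reading is a person's true mean plus error. The assumed mean / between-person SD / within-person SD are 70/9/6, 75/10/8 and 82/11/9 bpm. Let s = √(between² + within²), ρ = between²/s² and z = (100 − mean)/s. Table 6 is read literally: if the first reading is 100 or more, the third decides. One pre-dose occasion is modelled; filtering at the screening visit as well would lower the Day 1 figures somewhat.

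**How many enter on a repeat.** The probability of a high first and an acceptable third reading is P(first ≥ 100) − P(both ≥ 100), where the two are bivariate normal with correlation ρ. Divide by the probability of enrolling, P(first < 100) plus that difference, and multiply by 45.

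| Scenario | s | ρ | z | P(first ≥ 100) | P(both ≥ 100) | Difference | Share of enrolled | Of 45 |
|---|---|---|---|---|---|---|---|---|
| 70/9/6 | 10.82 | 0.69 | 2.77 | 0.0028 | 0.0005 | 0.0022 | 0.2% | 0.10 |
| 75/10/8 | 12.81 | 0.61 | 1.95 | 0.0255 | 0.0066 | 0.0189 | 1.9% | 0.86 |
| 82/11/9 | 14.21 | 0.60 | 1.27 | 0.1027 | 0.0404 | 0.0623 | 6.5% | 2.92 |

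A first reading of exactly 100 is out of range but ungraded. Counting only those whose first reading was 101 or more gives 0.07, 0.70 and 2.51 of 45. If sites stop at the first acceptable repeat, simulation gives 0.12, 1.02 and 3.70 entering on a repeat.

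**What happens to them afterwards.** In simulation under the literal rule, their later pulse exceeds the recorded baseline by about 1.5, 2.6 and 4.3 bpm with no treatment effect. At any one post-dose reading, about 11%, 17% and 25% of them are at 101 or more.

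**How much of the arm-mean shift is due to the repeats.** With no repeats allowed, truncating baseline at 100 already gives an apparent mean rise of (within²/s) × φ(z)/Φ(z). For 75/10/8 this is (64/12.81) × 0.0594/0.9745 = 0.30 bpm; for 82/11/9 it is 1.14 bpm. With the repeat rule, simulation gives 0.35 and 1.34 bpm. The eligibility limit therefore supplies 0.304/0.347 = 88% and 1.136/1.340 = 85% of the shift. In the 70/9/6 scenario both figures are about 0.03 bpm.

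**Systolic pressure.** With assumed 118/10/6, 122/12/8 and 128/14/10 mmHg, limits of 85 and 150, and stopping at the first acceptable repeat, 0.22, 1.19 and 3.67 of 45 enter on a repeat. Those repeated for a high value show a spurious later rise of 1.9, 3.6 and 5.7 mmHg.

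**The case against.** Several objections are sound and limit the point.

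- **Nothing says that only the qualifying reading is entered.** True. That is the natural reading of the sentence, but not its literal wording, and section 8 requires assessment data to be supported in source documents. The earlier readings are thus not destroyed; they need not reach the database from which listings and flags are made. Footnote d to Table 5 asks for information collected at the physical examination, vital signs included, to go into the eCRF, which sits awkwardly with Table 6.
- **A clinically relevant tachycardia has its own route.** Conditions present at consent go to medical history, and significant later findings are recorded as adverse events. This stands for real conditions, but it does not catch an isolated high reading that settles on repeat.
- **No stated analysis counts the value as new.** The treatment-emergent definition, which includes "events present prior to start of treatment but increased in severity on or after the dose of study medication based on preferred term", governs adverse events by preferred term, not raw readings, and shift tables are planned only for laboratory data. The harm is therefore to how listings, flags and individual events are read, not to a specified test.

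A reader might also infer more than the documents support:

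- **That systolic 141–150 mmHg before dosing disappears.** It does not. It is eligible, triggers no repeat and stays recorded. Diastolic pressure has no limit to trigger a repeat, and at the floor of 85 mmHg the rule selects upward.
- **That the comparison with placebo is biased.** Section 3 places eligibility before randomization and the rule is the same in all arms, so the expected between-arm difference is zero.
- **That the repeat rule drives the mean change.** As shown above, most of it comes from the eligibility limit.
- **That the qualifying reading is the analysis baseline.** The protocol does not say so, and that definition may properly sit in the analysis plan.

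**Conclusion.** The point holds as a minor defect in data capture. Table 6 lets an out-of-range pre-dose pulse, or a systolic pressure above 150 mmHg, stay out of the eCRF. Because all tachycardia grades lie above the pulse limit, a pulse graded before dosing can be shown as grade 0 at baseline, and the same value after dosing then looks like a new finding in the descriptive within-arm data.

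The expected number affected for pulse is about 0.1 to 3 of 45, or up to 3.7 if sites stop at the first acceptable repeat. These figures rest entirely on assumed means and standard deviations. The consequence is possible misreading of individual events. It is not a biased comparison with placebo, and the effect on arm means is small.

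**What to change.** Replace the last sentence of the Table 6 vital-signs row with one to this effect: all screening and Day 1 pre-dose vital-sign readings are entered in the eCRF, and the reading used for eligibility is flagged. The listings and abnormality flags in section 12.4.2 will then show out-of-range pre-dose values beside post-dose grades. The cost is up to two extra sets of entries per occasion for a few participants.

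The choice of analysis baseline can be left to the statistical analysis plan. Two tempting companion changes are better not made here. Using the first reading as baseline would give repeated participants a spurious fall of about 11 to 13 bpm in the scenarios above. Counting a post-dose grade as new only when it exceeds the worst pre-dose grade would set a single reading against the worst of up to three, which could hide a real signal.
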